#### Tertiary outcome measures

Quality of life will be assessed through mean improvement scores obtained from the generic short-form-12 (SF-12) questionnaire [37] and peripheral arterial disease specific Vascular Quality of Life Questionnaire-6 (VascuQoL-6) [38] at 3, 6, and 12 months from baseline between groups. SF-12 scale is a reduced version of the SF-36 questionnaire, easy-to-apply to assess the functional capacity of people over 14 years of age. It includes the following dimensions: physical role, body pain, mental health, general health, vitality, social function, and emotional role. In this case, we will use version 2, in which 50 (with an SD of 10) is taken as the mean of the general population. Values above 50 should be interpreted as best, while values below 50 should be interpreted as worse than the mean. For each of the items in each dimension, the score ranges from 0 (the worst health for that dimension) to 100 (the best health for that dimension). VascuQoL-6 questionnaire consists of six questions with a score of 1–4 in each question. To obtain the general score of the questionnaire, it is necessary to add all the points obtained in each question. A high final value indicates a better state of health. As there is no validated version in Spanish, our research group is performing a cross-cultural adaptation and validation of this questionnaire in Spanish.

### Adverse events

An adverse event (AE), also referred to as an adverse experience, can be any unfavorable and unintended sign (i.e., an abnormal laboratory finding), symptom, or disease temporally associated with the use of a drug (or other investigational therapy) and does not imply any judgment about causality. An AE can arise with any use of the drug (i.e., off-label use, use in combination with another drug and with any route of administration, formulation, or dose, including an overdose). A suspected adverse reaction (SAR) means any AR for which there is a reasonable possibility that the drug caused the AE. An AE is considered “serious” if (SAE), in the view of either the principal investigator, if it results in any of the following outcomes: death of subject; event with risk to life, that is, there was an immediate risk of subject death at the time the reaction was observed; hospitalization or prolongation of hospitalization; persistent or significant disability/incapacity; congenital anomaly; or birth defect or any other significant medical condition, i.e., important AEs that do not pose an immediate risk to life and do not result in death or hospitalization but may endanger the subject or may require intervention to prevent one of the outcomes listed. A suspected adverse reaction is considered “unexpected” if it is not listed in the safety reference information for the IMP or is not listed at the specificity or severity that has been observed or is not consistent with previously available, known risk information.

Causality and severity assessment of any occurring AE will be performed by the principal investigator. AE will be registered from administration of IMP to end of study visit. Investigator will actively ask patients about AE occurrence in every study visit. Also, AE may be spontaneously reported by the patients. All of them will be appropriately registered in the patient medical records. Only AR and SAE will be registered in eCRF and reported according to legal requirements. For the purposes of this study, proportion of amputations in each study group is a secondary outcome and will be registered specifically, so notification as SAE will not be performed unless its clinical course is different of more severe than expected.

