**Methods:**

A multicenter, randomized double-blind, placebo-controlled trial has been designed. Ninety eligible patients will be randomly assigned at a ratio 1:1:1 to one of the following: control group (*n* = 30), low-cell dose treatment group (*n* = 30), and high-cell dose treatment group (*n* = 30). Treatment will be administered in a single-dose way and patients will be followed for 12 months. Primary outcome (safety) will be evaluated by measuring the rate of adverse events within the study period. Secondary outcomes (efficacy) will be measured by assessing clinical, analytical, and imaging-test parameters. Tertiary outcome (quality of life) will be evaluated with SF-12 and VascuQol-6 scales.

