### Outcome measures

#### Primary outcome measure

Safety will be assessed comparing the rate of treatment related complications between groups (proportion of treatment related complications among groups) at 24 h and 3, 6, and 12 months from treatment administration, including those related with anesthetic procedure, IMP administration and those occurring after the procedure.

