#### Statistical analysis

Primary, secondary, and tertiary outcomes (safety, efficacy, and quality of life) will be assessed in intention to treat (ITT) and per protocol (PP) populations [39]. ITT population will include all patients who sign the informed consent and receive the investigational product. PP population will include patients who complete the 12-month follow-up period. A descriptive analysis of baseline characteristics of patients included in three groups will be performed. Quantitative variables will be expressed as mean and/or median and standard deviation and/or range. Qualitative variables will be expressed as percentages. When possible, the 95% confidence interval of each of the estimates made will be calculated. To analyze the primary outcomes, 24 h and 3, 6, and 12 months complication rates will be described and compared for the three groups using the Chi-square test or, if necessary, the Fisher exact test. The analyses of the secondary and tertiary outcomes will be performed as follows: qualitative variables will be described in terms of the percentage of improvement of the medical condition in each group and compared using the Chi-square test, or alternatively Fisher’s exact test. VAS scale, SF-12 scale, VascuQuol-6 scale, and the rest of the quantitative variables will be assessed by describing changes in variables at 3, 6, and 12 months from baseline, in an absolute and relative way. Changes at 3, 6, and 12 months in the three groups will be described and compared using the analysis of variance test, or the Kruskal-Wallis test, depending on whether or not the data follow a normal distribution. In all comparisons, a global comparison of the three groups and comparisons between groups by pairing will be carried out (low-dose treatment versus placebo, high-dose treatment versus placebo, high-dose treatment versus low dose, both treatment groups versus placebo). P values will be corrected by Bonferroni test. Regarding handling of missing data, a complete case analysis will be performed if percent of missing data is less than 5%. In another case, a data imputation will be performed for those variables with 25% or less missing values. Variables with more than 25% missing values will be removed from the analysis. The statistical analysis will be carried out by the statistical service of the Jiménez Díaz Foundation University Hospital. Data analyst will be blinded.

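### The primary safety outcome is worded in two ways, and the rule for what enters the eCRF and from when does not fully cover either

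*Protocol article*

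**What the plan says.** **Outcome.** The Abstract (Methods) states: "Primary outcome (safety) will be evaluated by measuring the rate of adverse events within the study period". The section Primary outcome measure states: "Safety will be assessed comparing the rate of treatment related complications between groups", at 24 h and 3, 6 and 12 months, "including those related with anesthetic procedure, IMP administration and those occurring after the procedure". The Statistical analysis section follows the second wording: "complication rates will be described and compared for the three groups using the Chi-square test", or Fisher's exact test where needed.

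**Capture.** The Adverse events section defines an adverse event without reference to cause. It fixes the window: "AE will be registered from administration of IMP to end of study visit". It has investigators ask about events at every visit and record all of them in the medical records, and then limits the trial database: "Only AR and SAE will be registered in eCRF and reported according to legal requirements". It frames a suspected adverse reaction by whether the drug may have caused it, and does not define an adverse reaction on its own.

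**Judgement.** "Causality and severity assessment of any occurring AE will be performed by the principal investigator". The section Blinding, randomization and allocation concealment provides two investigators per patient: an unblinded one who gives the treatment, and a blinded one who makes the assessments listed in Table 1. That table has an adverse events row marked from the treatment visit (V1) to month 12 (V5).

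**The concern.** Safety is the primary question of this trial, so the outcome definition, the capture rule and the recording window have to fit together. Here the two definitions count different events: one ignores causality and the other requires it. The capture rule and the window were not written to match either.

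For a non-serious event, the causality call decides whether the event enters the database at all. It should only decide how an entered event is classified. A doubtful call therefore cannot be re-examined in the trial dataset, and non-serious events cannot be compared by arm regardless of cause. Any event missed this way lowers the recorded complication rates. An analysis plan cannot repair this alone, because it can only analyse what was collected.

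**Working it through.** No arithmetic applies: the document states no event rate, effect size or power for the primary outcome, and says that no formal sample size calculation was made for it. The check sets each kind of event against the two definitions and the capture rule.

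| Kind of event | Counts under the Abstract | Counts under Methods | Reaches the eCRF as written |
|---|---|---|---|
| 1. Serious, any cause, from product administration on | Yes | If treatment related | Yes |
| 2. Non-serious, judged drug related, from product administration on | Yes | Yes | Yes |
| 3. Non-serious, judged unrelated, from product administration on | Yes | No | No, medical records only |
| 4. Non-serious, due to the anaesthetic, from product administration on | Yes | Yes | Only if an adverse reaction includes procedural reactions |
| 5. Anaesthetic complication before product administration | Yes, if the study period covers it | Yes | Not by the stated start; Table 1 could be read to include it |

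**Abstract definition.** Row 3 is enough. An all-cause rate needs these events, and the eCRF rule leaves them out. This follows from the text without further assumption.

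**Methods definition.** Rows 1 and 2 are covered. Row 4 depends on what an adverse reaction is. The Adverse events section ties suspicion to the drug; on that reading a non-serious anaesthetic complication is neither a reaction nor a serious event and is not entered. If the term is read to include reactions to the procedure, row 4 is covered and only row 5 remains.

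**Window.** Row 5 is an inference. The Interventions section places administration in the operating room after a presurgical assessment, and no section says when anaesthesia begins. Anaesthesia given for the injections must precede them, while registration opens at administration. Table 1 ticks adverse events for the whole of V1 (day 0), so practice on the day might cover this interval; the written start point does not.

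**Causality.** The adverse events row in Table 1 falls under the blinded investigator's assessments. The causality call belongs to the principal investigator. No sentence says that these are the same person.

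**Amputations.** They are recorded separately as a secondary outcome and are normally not notified as serious events. Whether they would count in an all-cause rate is not stated.

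**The case against.** The strongest reply is that the governing definition can be identified. The Abstract is shorthand, and the Methods and the analysis agree with each other. Under their definition the capture rule takes in drug-related and serious events, and what is left out is narrow. This stands in part: it reduces the problem under the Methods definition but does not close it, and the Abstract still names an outcome that the eCRF cannot supply.

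A reader might also infer more than the documents support:

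- *That the unentered events are lost.* They are not. All events go into the medical records, and the monitor may check data against the medical history. They are absent from the trial dataset as described.
- *That the randomised comparison is removed.* Serious events are entered whatever their cause, so they can still be compared by arm. Only the comparison of non-serious events is filtered by judgement.
- *That causality is judged unblinded.* The blinding section gives the Table 1 assessments to a blinded investigator and, after an unmasking, keeps those who evaluate the primary variable blinded. What is missing is only the link to the principal investigator.
- *That the loss of power can be stated.* Any figure would rest on an invented share of events captured, and would also have to allow for the planned Bonferroni correction.
- *That any-cause events must become primary.* Treatment-related complications are a legitimate primary outcome in phase II. In severely ill patients followed for 12 months, an any-cause outcome may have a high background rate that makes a given excess harder to detect.

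**Conclusion.** The point holds as a mismatch between outcome, capture rule and window. With high confidence, because it rests on explicit text: the primary outcome is worded in two ways, and the Abstract's version cannot be computed from the eCRF. With less confidence: the Methods version is also incomplete. That part assumes that an adverse reaction means a reaction to the drug (row 4), and that anaesthesia starts before the first injection while registration does not (row 5).

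Row 5 events precede the product and so cannot be caused by it. Missing them mainly understates the complication rates and should not, in expectation, favour one arm. The relatedness filter on non-serious events matters more for the comparison. The size of either effect cannot be estimated from the document. Since this is the primary outcome of a safety trial and the remedy is cheap while data are being collected, it should be corrected.

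**What to change.** 1. Use one primary definition in the Abstract, Methods and analysis. Treatment-related complications may stay primary; state whether anaesthetic and procedural reactions count as adverse reactions.
2. Enter all adverse events in the eCRF, with flags for seriousness and relatedness, so that an all-cause comparison by arm is available as a supportive analysis. State whether amputations count in it.
3. Open adverse event registration at the start of anaesthesia, and make the Adverse events section and Table 1 agree.
4. State that the causality call assigned to the principal investigator is made by the blinded investigator.

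The cost is a wording change and modest extra data entry. Events are already asked about and written in the medical records, at no more than 90 patients × 5 marked visits (V1 to V5) = 450 patient-visits. Retrieving the same events later from the records of ten hospitals would cost more.

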### Statistical considerations

#### Sample size calculation

A formal size calculation based on the expected differences for the primary outcome has not been performed. This is a phase II, dose-finding study, and no previous data on the preliminary efficacy of Ad-MSC with CLI including type 2 DM patients are available to date. A sample size of 30 patients per group was deemed appropriated based on the possibility to reach normality and the feasibility to recruit 90 eligible patients in 10 university hospitals.

#### Data collection and management

Relevant information for the study will be registered in electronic medical records and then entered in the eCRF in a pseudonymized fashion. All of these data will be also documented in the investigator’s file, which will be saved in key-locked cabinets. Monitor may need to verify the original data against the subject’s medical history and sponsor will have access to the final trial dataset.

#### Statistical analysis

Primary, secondary, and tertiary outcomes (safety, efficacy, and quality of life) will be assessed in intention to treat (ITT) and per protocol (PP) populations [39]. ITT population will include all patients who sign the informed consent and receive the investigational product. PP population will include patients who complete the 12-month follow-up period. A descriptive analysis of baseline characteristics of patients included in three groups will be performed. Quantitative variables will be expressed as mean and/or median and standard deviation and/or range. Qualitative variables will be expressed as percentages. When possible, the 95% confidence interval of each of the estimates made will be calculated. To analyze the primary outcomes, 24 h and 3, 6, and 12 months complication rates will be described and compared for the three groups using the Chi-square test or, if necessary, the Fisher exact test. The analyses of the secondary and tertiary outcomes will be performed as follows: qualitative variables will be described in terms of the percentage of improvement of the medical condition in each group and compared using the Chi-square test, or alternatively Fisher’s exact test. VAS scale, SF-12 scale, VascuQuol-6 scale, and the rest of the quantitative variables will be assessed by describing changes in variables at 3, 6, and 12 months from baseline, in an absolute and relative way. Changes at 3, 6, and 12 months in the three groups will be described and compared using the analysis of variance test, or the Kruskal-Wallis test, depending on whether or not the data follow a normal distribution. In all comparisons, a global comparison of the three groups and comparisons between groups by pairing will be carried out (low-dose treatment versus placebo, high-dose treatment versus placebo, high-dose treatment versus low dose, both treatment groups versus placebo). P values will be corrected by Bonferroni test. Regarding handling of missing data, a complete case analysis will be performed if percent of missing data is less than 5%. In another case, a data imputation will be performed for those variables with 25% or less missing values. Variables with more than 25% missing values will be removed from the analysis. The statistical analysis will be carried out by the statistical service of the Jiménez Díaz Foundation University Hospital. Data analyst will be blinded.

So far, no plans to use data generated in this trial for additional studies is foreseen. Nevertheless, and according to GDPR requirements, a statement has been included in the informed consent form informing the patient about this possibility and asking her/him for permission.

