**Fig. 1 Fig1:**
[figure not shown]
Flowchart: 90 patients will be recruited in the study and randomly allocated to three groups (high-dose group = 30; low-dose group = 30; control group = 30). The assessment will be done 24 h and 3, 6, and 12 months, respectively

**Table 1 Tab1:** Schedule of study procedures

	Study period						
	Enrolment		Treatment	Follow-up			
Timepoint	***V-1, selection visit***	***V0, baseline visit***	V1, treatment	***V2, 24 h***	***V3, 3 m***	***V4, 6 m***	***V5, 12 m***
	***Day − 30 to day − 21***	***Day − 20 to − 1***	Day 0	***Day 1***	***Day + 90 ± 7***	***Day + 180 ± 15***	***Day + 365 ± 15***
***Eligibility criteria***	X	X					
***Informed consent***	X						
***Anamnesis***	X						
***Physical examination***	X		X	X	X	X	X
***Blood test***	X				X	X	X
***Urine pregnancy test***	X						
***Rutherford-Becker category***	X						
***Ankle-arm index***	X				X	X	X
***Ulcers evaluation (Wifi classification)***	X				X	X	X
***VAS scale***	X			X	X	X	X
***Gastrocnemius muscle perimeter***	X				X	X	X
***Temperature of the limb***	X				X	X	X
***Neuropathic symptoms***	X				X	X	X
***Quality of life scales (SF-12 and VascuQol-6)***	X				X	X	X
***MRI***	X						X
***Randomization***		X					
***Pre surgical evaluation***		X					
***Treatment administration***			X				
***Concomitant medication***	X	X	X		X	X	X
***Adverse events***			X	X	X	X	X

*MRI* magnetic resonance imaging, *h* hours, *m* month, *v* visit

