### Blinding, randomization and allocation concealment

Masking of participants will be guaranteed as follows: the solution for intramuscular infusion of Ad-MSC (active treatment) will have the same aspect as HypoThermosolFRS (placebo), and the syringes will be identified by a label that will exclusively contain the information corresponding to the clinical trial and the patient code. However, since the density of each product may be different, it is assumed that there is a risk that the clinical investigator administering the treatment may know which treatment is being applied. For that reason and to ensure double blind, each center will count, as a minimum, with two investigators per enrolled patient: a non-blinded investigator who will administrate cellular therapy and a blinded investigator who will perform the assessment of participants as described in Table 1. Randomization will be performed through the electronic case report form (eCRF). Study subjects will be assigned to group 1, 2, or 3, at a ratio 1:1:1, based in a random block sequence prepared by the sponsor’s statistical service. The assigned group information from each participant will not be visible in the eCRF. Then, an email with the assigned treatment group information of the participant will be sent automatically to non-blinded team. No stratification process has been designed in the randomization scheme. If a phase III clinical trial is subsequently developed, stratification will be defined, according to preidentified factors that could influence efficacy outcomes. During the study, masking can be broken in the event of a serious adverse event (SAE) related to the study medication that requires urgent medical treatment. The researcher will notify the sponsor within a maximum period of 24 h and sign the SAE notification form that will be sent by fax or email to the person in charge of pharmacovigilance of the study. The sponsor will communicate to the investigators any information that may affect the safety of the trial subjects as soon as possible. In the event of unmasking, blinding will be maintained for those responsible for evaluating the primary variable and for those responsible for data analysis and interpretation of the results.

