### Interventions

Ad-MSC will be obtained from young healthy donors who previously gave their informed consent. Good manufacture practice (GMP)-accredited cell therapy laboratories from University of Navarra Clinic and from Salamanca University Hospital will be responsible of the master cell bank (MCB). MCB is the system whereby successive batches of the cell therapy product are manufactured by isolation and expansion of cells derived from a single adipose tissue sample. In this way, we ensure stability and uniformity in the treatment. MCB laboratories will send batches of cryopreserved cells to working GMP cell bank (WCB) laboratories. When a participant of the study is assigned to active treatment group, the sponsor will notify the assigned WCB laboratory to thaw and culture the cells in one passage. Finally, the batch will be packaged, labeled, and sent to the pharmacy service of the corresponding hospital (see Figs. 2 and 3). Three parallel groups have been designated as follows:
*Group 1*. Control group (*n* = 30). Placebo will consist of HypoThermosolFRS contained in an identical vial to that of the investigational medicinal product (IMP) and with the same volume.*Group 2*. Low-cell dose treatment group (*n* = 30). This group will receive a single intramuscular administration of 1 × 10^6^ cells/Kg weight.*Group 3*. High-cell dose treatment group (*n* = 30). This group will receive a single intramuscular administration of 2 × 10^6^ cells/Kg weight.

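### The set called ITT holds only dosed patients, and the set called PP holds only 12-month completers yet is applied to the primary safety outcome

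*Protocol article*

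**What the plan says.** All on this point is in the protocol article.

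- **Statistical analysis**, first set: "ITT population will include all patients who sign the informed consent and receive the investigational product".
- **Statistical analysis**, second set: "PP population will include patients who complete the 12-month follow-up period". No other condition is given for it.
- **Statistical analysis**, where they apply: "Primary, secondary, and tertiary outcomes (safety, efficacy, and quality of life) will be assessed in intention to treat (ITT) and per protocol (PP) populations".
- **Primary outcome measure**: "Safety will be assessed comparing the rate of treatment related complications between groups", at 24 h and 3, 6 and 12 months. Complications of the anaesthetic procedure are counted explicitly.
- **Table 1**: randomisation and the presurgical evaluation are marked under "V0, baseline visit" (day −20 to −1). Treatment is at V1 (day 0).
- **Interventions**: manufacture for the patient begins after allocation, and only in the active arms. Once an active arm has been allocated, "the sponsor will notify the assigned WCB laboratory to thaw and culture the cells in one passage". The same section provides for withdrawal when a clinically relevant condition puts the patient at risk.
- **Blinding, randomization and allocation concealment**: after randomisation, "an email with the assigned treatment group information of the participant will be sent automatically to non-blinded team".

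**The concern.** Intention to treat means that everyone randomised is analysed in the arm assigned. Here membership depends on receiving the product, which happens up to 20 days after randomisation. A randomised patient who is not dosed is in no planned efficacy or quality-of-life analysis unless followed to 12 months undosed. The groups compared are then no longer the groups that randomisation created.

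The PP set has a different fault. Its single condition is reaching 12 months, so it is a completers' set with no reference to adherence. An adherent patient who dies in month 2 is out, and a patient with a serious deviation who completes is in. Applied to the primary outcome, it conditions a safety rate on having survived and stayed in the trial. A patient with a complication at 24 h who later dies or is withdrawn is missing from the 24 h, 3 month, 6 month and 12 month PP rates alike.

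**Working it through.** The article gives no rate for non-treatment, death, dropout or complications, and it states that no formal sample size calculation was done. So there is no figure of its own to reproduce beyond 3 × 30 = 90, which agrees. The definitions can be checked by reading them against the schedule. The rates below are assumptions.

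**1. Is receipt of product a post-randomisation event?** Yes. Randomisation is at V0 (day −20 to −1) and dosing at V1 (day 0).

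**2. Can non-receipt differ by arm?** It may. Thaw and culture are needed only in the active arms and start only after assignment, so a failed batch can affect only those arms. A failed presurgical assessment or deterioration while waiting can affect any arm, because all arms share the same window and the same assessment.

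**3. What could this do to a response rate?** Assume a 30% response in every arm and no treatment effect.

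- Loss unrelated to prognosis: the rate stays at 30%.
- 10% of an active arm undosed, none of whom would have responded: 0.30 / 0.90 = 33.3%.
- 15% undosed, none of whom would have responded: 0.30 / 0.85 = 35.3%.

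The last two are worst cases. With equal, similarly selected loss in all arms, no between-arm difference arises.

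**4. Is a treated set suitable for safety?** Essentially yes. One group is left out: patients whose anaesthetic complication prevents injection. They never receive the product, so they are not in the first set. They would be in the second only if followed to 12 months undosed, for which the article makes no provision. The Primary outcome measure section nevertheless counts anaesthetic complications.

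**5. What does the completers' set do to a complication rate?** Let p be the true rate, a the proportion lost before 12 months among patients with a complication, and b the proportion lost among those without:

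PP rate = p(1 − a) / [p(1 − a) + (1 − p)(1 − b)]

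With p = 0.20:

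| a | b | Calculation | PP rate |
|---|---|---|---|
| 0.20 | 0.20 | 0.16 / (0.16 + 0.64) | 20.0% |
| 0.20 | 0.10 | 0.16 / (0.16 + 0.72) | 18.2% |
| 0.50 | 0 | 0.10 / (0.10 + 0.80) | 11.1% |

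**6. And to a difference between arms?** Assume true rates of 10% (control) and 30% (high dose), a difference of 20 points:

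| a | b | Control | High dose | Difference (points) |
|---|---|---|---|---|
| 0.20 | 0.20 | 10.0% | 30.0% | 20.0 |
| 0.30 | 0.10 | 0.07/0.88 = 8.0% | 0.21/0.84 = 25.0% | 17.0 |
| 0.50 | 0.10 | 0.05/0.86 = 5.8% | 0.15/0.78 = 19.2% | 13.4 |
| 0.70 | 0.10 | 0.03/0.84 = 3.6% | 0.09/0.72 = 12.5% | 8.9 |

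In these scenarios the completers' set understates both the rates and the difference once patients with complications are lost more often. With loss unrelated to complications it does not.

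**The case against.** The best defence is that the primary outcome is already to be analysed in all treated patients, which is the conventional safety set. The PP result stands beside that analysis and does not replace it. The trial is phase II, efficacy is described as preliminary, and the Recruitment of eligible participants section does not expect high dropout. Most of this stands. For safety the first set is mainly a mislabel, and the effect may be small, although with 30 per arm each lost patient is 1/30 = 3.3% of an arm. The defence does not make a completers' rate a valid safety rate, and it does not supply an intention-to-treat analysis of efficacy.

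A reader might go further on three points, and the article does not support them.

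- *Losses before dosing fall only on the active arms and favour the cells.* Only batch failure is confined to those arms. The batches come from banked healthy-donor cells, so a failure has no evident link to the patient's prognosis. It may cost patients without biasing the comparison.
- *The unblinded team can select who is dosed.* The article has the non-blinded investigator administer the treatment and gives assessment to a blinded one. The MRI reader and the data analyst are also blinded. Nothing says that the non-blinded team decides whether a patient is dosed.
- *The article should name the leading set and list the deviations that exclude a patient from PP.* Both are commonly left to the statistical analysis plan, so their absence here is no fault. The printed definitions themselves are the problem.

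**Conclusion.** The point holds in three parts.

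1. **Efficacy and quality of life:** the set labelled ITT is a treated set, and no all-randomised set is defined. Whether this biases the comparison, in which direction and by how much cannot be determined from the article. The shift from 30% to 33.3% or 35.3% is a worst case that assumes no undosed patient would have responded and that losses fall on an active arm.
2. **Safety, treated set:** appropriate apart from its name and the omission of patients whose anaesthetic complication prevents injection.
3. **Safety, PP set:** unsuitable at every time point. For an assumed true rate of 20%, it reports from 20% (loss unrelated to complications) through 18.2% to 11.1% (half of those with a complication lost and nobody else). The distortion depends wholly on how far complications lead to death or withdrawal. The withdrawal rule makes that link plausible, but the article does not quantify it.

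**What to change.** - Define ITT as all randomised patients analysed in the arm assigned, and use it for efficacy and quality of life.
- Rename the present treated set the safety set and define it as all patients in whom the procedure was started, grouped by product received. Analyse the primary outcome there, counting events up to death or withdrawal.
- Do not analyse safety in completers. Define PP by adherence to the protocol and not by reaching 12 months, and use it only as support for efficacy.

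The redefinition takes a few sentences, but it has consequences. Undosed patients need outcome follow-up or explicit missing-data handling, because they will count towards the 5% and 25% thresholds in the Statistical analysis section. They may also dilute the efficacy estimate slightly. The Adverse events section starts recording at administration of the product, so the recording window should open at the start of the procedure to match the new safety set. The change should be made before unblinding.
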